### Sample size and power

The minimum sample size (*N)* required for DCEs can be calculated as *N≥ (500 x c)/(TxA)*, where T is the number of included choice sets, A is the number of alternative profiles per set, and c is the number of analysis cells (attributes). C can be equal to the greatest number of levels for any attribute to assess main effects [31, 73]. The final DCE includes 8 choice sets (T), 7 attributes, 6 levels (C) and 3 alternatives (including the opt out option; A); the minimum number of participants needed is n = 125. To explore heterogeneity by factors such as sex, age, or residence, to increase the statistical power of our analyses, and to mirror other DCE studies [31], our aim is to recruit a larger sample size.

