### Sample size and inclusion criteria

Participants in all phases of the study will be adult Samoans (30 to 80 years) recently diagnosed with diabetes (<12 months for the pilot, <24 months for the finalized implementation) who provide permission to access their medical records and are willing to provide written informed consent for study participation. Twenty participants completed semi-structured interviews and were administered the pilot DCE (completed July 2023). Following refinement of the instrument, the finalized DCE survey is now being administered to n = 450 Samoan adults living with diabetes, along with associated questionnaires and anthropometric measures (initiated August 2023). Baseline recruitment is expected to be completed by July 2024. Two hundred and twenty participants will complete additional DCEs at 12- and 24-months post baseline assessment (Fig 2). Potential participants will be excluded if they are unable or unwilling to complete study protocols and/or were only diagnosed as having gestational diabetes (given the unique healthcare needs of pregnancy). Equal numbers of men and women (50.0%) will be recruited for each phase of the study. Participants will be recruited from regional Ministry of Health run regional hospitals and clinics throughout the islands of ’Upolu and Savai’i, and the diabetes specialty care clinic located centrally in Apia. Participants will also be recruited using the Obesity Lifestyle and Genetic Adaptations (OLaGA) Research Center’s social media page (>9,700 followers). The OLaGA Research Center is a collaboration between Yale and Brown Universities and the Samoan Ministry of Health. After determining eligibility, Samoan Research Assistants (RAs) will introduce the study objectives to the participants. Before each study assessment, written informed consent will be obtained from each participant.

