### Choice set design, and preference elicitation

A ‘Best-Best’ DCE was constructed (*preference elicitation)*. Best-Best DCEs elicit additional preference information, are designed to inherently rank choices, and increase the statistical power for analyses [72–74]. Participants are being presented with a series of choice sets, each with three different alternative care profiles (one of which will always be an ’opt-out/none of these’ for each attribute). Each profile presents a hypothetical scenario (comprised of combinations of attributes and levels) for diabetes care. Participants are asked to choose their most preferred option from the three profiles, followed by their second preference (but not worst) from the remaining alternatives. Because treatment protocols vary by patient, it was challenging to identify a true ’standard care’ level for each attribute. Frequently cited experiences (e.g., only being able to see the first available doctor) were included as potential levels in the design of the instrument and are intended to represent attribute levels generally (but not inclusive to all) experienced by patients. Our aim in doing so is to facilitate a comparison of the preferences for alternative options compared to these commonly experienced encounters; additionally, the inclusion of an opt-out option, provides better representation of real-world scenarios [72].

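### The stated minimum of 125 counts the opt-out as a profile; with the two profiles that carry attribute levels, the article's own formula gives 188

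*Protocol article*

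**What the plan says.** The section on sample size and power gives a rule of thumb, N ≥ 500c/(T × A), "where T is the number of included choice sets, A is the number of alternative profiles per set". For c it adds: "C can be equal to the greatest number of levels for any attribute to assess main effects". The inputs follow: "The final DCE includes 8 choice sets (T), 7 attributes, 6 levels (C"), and then "3 alternatives (including the opt out option; A); the minimum number of participants needed is n = 125". The inclusion of the opt-out in A is therefore explicit.

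The section on choice set design and preference elicitation describes the sets as "each with three different alternative care profiles (one of which will always be an ’opt-out/none of these’ for each attribute"). It then explains that a profile is a hypothetical care scenario built from attributes and levels.

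The planned numbers are 450 at baseline and a subset of 220 for the later surveys. On the subset, the section on sample size and inclusion criteria says "Two hundred and twenty participants will complete additional DCEs at 12- and 24-months post baseline assessment". The implementation section says only that 220 will be asked to do so.

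**The concern.** The formula divides by T × A, the number of profiles each participant sees. Rearranged, it asks for N × T × A/c ≥ 500. When c is the number of levels of the largest attribute, the left side is the number of times each level of that attribute is displayed across the whole sample. An alternative that shows no level cannot add to that count.

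By the article's own description, one of the three alternatives is of this kind. Counting it credits each participant with 24 level displays per attribute when only 16 occur, and the stated minimum comes out a third too low.

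At stake is the only sample-size benchmark in the article. Anyone who checks the number of completers against it, at baseline or at a later wave, would be using a floor that is too low.

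**Working it through.** **Inputs** (protocol article)
- c = 6, T = 8, A = 3 with the opt-out counted: sample size and power.
- Two level-bearing profiles plus one opt-out per set: choice set design and preference elicitation.
- Baseline 450; follow-up 220 at 12 and 24 months: sample size and inclusion criteria, and implementation.
- Level balance: the choice set section says that levels appear equally often.
- Expected attrition: mentioned in the planned analyses, but without a figure.

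**Step 1. Reproduce the stated figure.**
500 × 6/(8 × 3) = 3000/24 = 125. This matches exactly. Taking c as the seven attributes would give 500 × 7/24 = 145.8, so 146. The 125 therefore rests on c = 6 and A = 3.

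**Step 2. Count only the alternatives that show levels.**
500 × 6/(8 × 2) = 3000/16 = 187.5, rounded up to 188.
188/125 = 1.50, so the corrected figure is 50% higher.

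**Step 3. Check against displays per level, N × 8 × 2/6.**

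| N | Displays per level of the six-level attribute |
|---|---|
| 125 | 333 |
| 188 | 501 |
| 220 | 587 |
| 450 | 1200 |

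**Step 4. Compare with the planned numbers.**
- Baseline: 450/188 = 2.4.
- Follow-up: 220 − 188 = 32 to spare, and 32/220 = 14.5%. Against 125 the apparent margin would be 95/220 = 43.2%.

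If 220 is the number invited, the number left depends on an attrition rate that the article does not give. Over an assumed range:

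| Assumed loss | Remaining of 220 | At least 188? |
|---|---|---|
| 5% | 209 | yes |
| 10% | 198 | yes |
| 15% | 187 | no, by one |
| 20% | 176 | no |

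If 220 is the number of completers, the minimum of 188 is met and this table does not apply.

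**The case against.** **A = 3 follows the article's own label.** The choice set section calls all three alternatives care profiles, and the sample-size section says openly that the opt-out is included. The division is correct for the A that was used, and the choice is disclosed. But the label does not fit the description that follows it, in which a profile consists of attributes and levels. A none-of-these option has neither. Nor can it stand in for a usual-care option with levels: the article says that commonly experienced care was put into the design as attribute levels, and treats the opt-out separately.

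**The meaning of 500 is inferred.** The article does not say that the rule counts displays per level, and the sources it cites for the rule are not at hand. This stands as a caveat. The reading does, however, follow directly from rearranging the formula with c as defined.

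**The Best-Best format yields more information than the rule credits.** Each set gives a first and a second choice, so 188 may be conservative. That is fair, but the formula has no term for ranking. The second choice is made among the alternatives left from the same set, so no new profile is displayed. It is no reason for A = 3.

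**Nothing was sized on 125.** This stands, and it limits the weight of the point. The article treats 125 as a floor and recruits well above it.

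**Stronger readings that the documents do not support.** A reader might infer that the follow-up is undersized. The article never justifies 220 by this rule, 220 exceeds 188, no attrition rate is given, the longitudinal analyses are described as largely exploratory, and a repeated cross-sectional approach is named in case losses are heavier than expected. A reader might also multiply c by the number of subgroups, because the larger sample is meant in part "To explore heterogeneity by factors such as sex, age, or residence", and conclude that some subgroup analyses fall short. The article ties c to main effects and never extends it in that way. It gives residence only as an example, and it does not specify an analysis that crosses region with the six-level attribute.

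**Conclusion.** The stated minimum is wrong by the article's own formula and its own description of the choice sets: 188, not 125. The stated figure is one third below the unrounded 187.5. This rests on three assumptions: that the opt-out shows no attribute levels, as the article says; that levels are balanced, as it also says; and that the rule concerns displays per level, which follows from its algebra.

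This is a minor correction to a stated figure. Main effects at baseline are not in doubt under this rule. At follow-up the rule is met as long as at least 188 people complete each wave, which allows up to 14.5% loss if 220 is the number invited. Whether that margin is narrow cannot be judged without an expected attrition rate. Both 125 and 188 are rule-of-thumb floors for main effects, not power calculations.

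**What to change.** In the section on sample size and power, define A as the number of alternatives that show attribute levels, set A = 2, and restate the main-effects minimum as n = 188. Add a sentence saying that 450 at baseline clears this comfortably and that 220 at follow-up clears it while at least 188 complete each wave. Reconcile the two statements about the 220, so that it is clear whether they are invited or expected to complete.

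The cost is a few lines of text. The published minimum becomes less favourable. Enrolment, the instrument and the planned models do not change.

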### Dissemination of results

Results of the study will be presented to participants and the Samoan Ministry of Health upon completion of the study. Additionally, we will disseminate the findings to peer-reviewed journals. We plan to use a staged narrative approach to disseminate the findings. Interview data will be published upon analysis [28]. Integration of the qualitative and qualitative results will likely occur in the quantitative-focused papers following the analysis of the DCE (using a narrative weaving approach to report on the findings of the interviews and DCE while also mapping how the DCE attributes corresponded to the interview responses [28]). We plan to also incorporate joint displays [28] to integrate the qualitative and quantitative data to present the results at academic conferences and invited seminars.

### Project status and ethical considerations

This project has received ethical approval from the Yale Institutional Review Board (Yale IRB 2000031387; 2000032062) and the Health Research Committee at the Samoan Ministry of Health. Enrollment for the finalized baseline DCE assessment was initiated August 2023 (Fig 2).

### Inclusivity in global research

Additional information regarding the ethical, cultural, and scientific considerations specific to inclusivity in global research is included in the supporting information section (S1 Checklist).

## Discussion

Effective engagement in care is critical to reduce the physiological, economic, and social burdens of diabetes [2, 3, 93]. In Samoa, however, patient preferences for diabetes care or how care can be best optimized to facilitate patient retention is understudied. The present protocol aims to address this knowledge and practice gap and inform future diabetes care approaches. By conducting a DCE, we will be able to identify and quantify preferences Samoan adults living with diabetes have regarding their diabetes care and provide policy-relevant estimates of their willingness to pay for and engage in these services.

The timing of this study and its expected outputs are aligned with the implementation of a World Bank-funded, five year, NCD-focused health system strengthening project [94] and the development of the next Samoa National NCD policy [95], in which the government plans to invest heavily in preventative care strategies and secondary prevention. This project will provide vital information regarding the design of diabetes care programming options that may increase the likelihood of care engagement and retention. Samoan leadership in regional NCD networks means that the methodological approach and results of the work can be shared to shape regional practice and policy throughout the Pacific and beyond. Given that Samoan cultural traditions and behavioral norms are shared among Samoans throughout the diaspora (and many Pacific Islanders more broadly) we expect that our results may also be applicable and integral to reducing the high and disproportionate burden of diabetes experienced among Samoan and Pacific Islander populations [96–99]. Our work aims to identify critical, evidence-based, and culturally acceptable care solutions that will engage and retain diabetes patients in treatment and provide them with greater agency in their disease management.

We recognize several potential limitations to the presented protocol. As a survey-based method, DCEs are limited in their ability to capture the individualized lived experiences of having diabetes and/or the more comprehensive litany of preferences that people living with diabetes have regarding their care. Nonetheless, we believe that the potential this method holds for providing novel and representative information about diabetes care preferences in the country transcends its limitations. Additionally, by using semi-structured interviews to design the instrument, our aim was to capture potential Samoan-specific preferences for care that will facilitate the ultimate construction and adaptation of locally relevant treatment options. We are also restricting our sample to individuals recently diagnosed with diabetes to control for changes in care preferences related to disease duration and progression [36, 100]. While our longitudinal analyses aim to capture how care preferences may change over time, a longer time examination of those preferences is needed.

The approach described here is designed to generate impactful, policy and practice-relevant data using a discrete choice experiment. The results obtained will provide important documentation of diabetes care preferences among Samoans. These findings have the potential to shape diabetes treatment design, adaptation, and implementation within high-need settings and among high-risk populations.
